## Abstract

Maternal immunisation, a low cost and high efficacy intervention is recommended for its pathogen specific protection. Evidence suggests that maternal immunisation has another significant impact: reduction of preterm birth (PTB), the single greatest cause of childhood morbidity and mortality globally. Our overarching question is: how does maternal immunisation modify the immune system in pregnant women and/or their newborn to reduce adverse pregnancy outcomes and enhance the newborn infant’s capacity to protect itself from infectious diseases during early childhood? To answer this question we are conducting a multi-site, prospective observational cohort study collecting maternal and infant biological samples at defined time points during pregnancy and post-partum from nulliparous women. We aim to enrol 400 women and determine the immune trajectory in pregnancy and the impact of maternal immunisation (including influenza, pertussis and/or COVID-19 vaccines) on this trajectory. The results are expected to identify areas that can be targeted for future intervention studies.

## Introduction

Globally, preterm birth (PTB) remains one of the most significant causes of death and morbidity in childhood (1, 2). PTB is the single most important cause of death in children under five years of age, with one million children dying each year due to PTB-related complications (1). It is also an important cause of disability and major contributor to health care expenditure (3). Most PTB and stillbirths occur in low-income settings, with over 75% of cases occurring in Asia and sub-Saharan Africa, and morbidity and mortality rates of premature infants in these settings remain disproportionately high (1). Despite efforts to reduce PTB worldwide, rates of this adverse pregnancy outcome remain persistently elevated, independent of income setting (4, 5). Hence, there is an urgent need for more effective interventions to reduce PTB and its attendant neonatal and early childhood morbidity and mortality, particularly in low- and middle-income countries (LMICs).

Maternal vaccines are a well-established strategy used for prevention of pathogen-specific disease in mothers and infants through transplacental transfer of maternal antibodies. Routine tetanus toxoid-containing vaccination was the first routine immunisation program implemented for pregnant women (6). Beyond pathogen-specific benefits, some studies have also identified pathogen-agnostic or non-specific effects (NSE) of maternal vaccination protecting against several adverse birth outcomes, including PTB and stillbirth (7–11). Our group have previously published a systematic review of the safety of influenza vaccination in pregnancy (12). An unexpected finding of our review of the literature was an association between maternal immunisation and lower rates of PTB (12). However, this finding has not been consistent across other published studies. Nonetheless, we were intrigued by the possibility of immunisation being associated with reduced PTB and thus proceeded to explore this association in a large dataset of 270,851 women who gave birth in the Australian state of Victoria between Jan 2015 and Dec 2018 (11). We found that women receiving influenza vaccine and/or pertussis containing vaccine during pregnancy had a significantly lower risk of PTB than unvaccinated women (11). Further, the reduction in PTB we observed in association with maternal vaccination remained significant and consistent across four different influenza seasons (2015-2018) and across different times of the year (during and outside of influenza seasons) (11). The benefits therefore were unlikely related to preventing maternal infection or actual exposure to influenza virus. We have further confirmed this association when accounting for immortal time bias (13).

The term pathogen-agnostic or NSE of vaccination aims to capture protection against outcomes unrelated to prevention of the intended vaccine preventable disease (14). We will use the term NSE for the remainder of this article. These could theoretically be associated with any vaccine. A systematic review in 2016 sponsored by the World Health Organization concluded that the Bacille Calmette-Guerin (BCG) vaccine and measles vaccine were associated with mortality benefits greater than expected based on pathogen-specific effects alone (15). For example, although *Mycobacterium tuberculosis* is the intended target pathogen of BCG vaccines, BCG vaccination of newborns reduces risk for death from a wide range of infections unrelated to tuberculosis, including neonatal sepsis (16, 17). Mechanisms that have been postulated include changes in innate immunity, including a rapid increase in neutrophils (18).

Although the causes of PTB are not entirely understood, there are several risk factors and mechanisms that are known to be implicated in the process (19). Some studies suggest that in the case of preterm labour, multiple factors contribute to dysregulated inflammatory processes that result in early initiation of labour (19, 20). This trajectory, down an unfavourable path, may be underpinned by activity of the immune system- the so called “immune trajectory” in pregnancy. One hypothesis for the NSE of maternal immunisation on birth outcomes is that maternal vaccines may modulate the maternal and fetal immune trajectory such that these heightened inflammatory processes that contribute to PTB are reduced. Similar to the benefit of BCG on newborn host defence, maternal vaccination could for example activate innate immunity providing broad protection against pathogens, or enhance immune regulatory pathways, which together could reduce potentially harmful inflammatory responses during pregnancy (21, 22).

NSE of vaccination are increasingly being recognised for their health benefits in postnatal life. Yet, this has never been explored in prenatal life, i.e. during pregnancy. Our and others’ data indicate that maternal immunisation may increase immune resilience leading to longer gestation, and in turn, a healthy start to life. For the purpose of this study, we define “immune resilience” as the capacity to preserve and/or rapidly restore immune function that resist adverse outcomes and control other causes of inflammatory stress. Based on the above observations, and the clear need to understand mechanisms for other vaccines and interventions to tackle the substantial burden of adverse pregnancy outcomes, we designed the PREMITUR study.

## Aim and hypothesis

The PREMITUR study hypothesises that maternal immunisation alters the immune trajectory in pregnant women in a way that leads to a reduction in adverse pregnancy outcomes. The specific aims of our study are:

Aim 1. To determine the immune trajectory of pregnancy that leads to term versus PTB.Aim 2. To define the impact of maternal immunisation on the immune trajectory of pregnancy.Aim 3. To delineate the impact of maternal immunisation on the immune trajectory of the infant.

## Rationale

Pregnancy induces rapid changes in systemic maternal immunity. In healthy term pregnancy these changes follow a healthy developmental trajectory (23–25), while the final common pathway leading to adverse pregnancy outcome appears to involve an altered immune trajectory (26). However, the immune trajectory of pregnancy in relation to adverse pregnancy outcomes has not been comprehensively captured via the powerful integration across the range of biological domains that we will conduct here (RNA, protein, metabolite, function – ‘multi-omics’). To our knowledge, there is only one recent publication that applied a similar integrated, multi-omic approach to PTB (27). While this published report clearly confirms feasibility and advantages of our systems biology approach, the previous study only assessed a single time point in a cross-sectional design, i.e. they did not attempt to determine the trajectory (27). And importantly, this published report did not take the impact of maternal immunisation into account. We have recently shown that integrating across the multi-omic space and conducting these assessments longitudinally over time in the same subject allows delineation of developmental trajectories that provide critical insight into complex biological processes (18, 28). Importantly, this integration across biology (multi-omics) and over time in the same subject allows for sound and rigorous statistical interrogation of group sample sizes with n ≤20 (18, 25).

Our group has also recently shown that one’s “immune baseline” can determine the outcomes of vaccination or infection (29, 30), and that for the immune trajectory of the newborn this ‘baseline’ is influenced by maternal immunity (31, 32). We have also shown that the ‘baseline’ in early life is not a stable steady state (as it is in adults), but a dynamic yet highly predictable (and predictive) trajectory (28). This suggests that impacting the mother’s immune trajectory in pregnancy through maternal immunisation may impact the immune trajectory of the infant. The concept of maternal immunity impacting immune ontogeny of her infant is already widely accepted for maternal antibodies influencing the infant’s antibody response to vaccination (33). But there is growing evidence that this mother-infant interaction goes far beyond adaptive immunity: i) maternal quadrivalent influenza vaccine (QIV) reduces acute airway infections in the infant beyond influenza (34) which may relate to vaccine-induced cytokine responses in the nasal mucosa of her infant (35); ii) maternal diphtheria, tetanus and acellular pertussis (dTpa) immunisation during pregnancy reduces the risk for acute airway infections beyond Bordetella pertussis in infants, which may relate to vaccine-induced cytokine transfer across the placenta (36). The theoretical underpinnings of our rationale for Aim 3 are thus supported by existing evidence. What is lacking is evaluation of the maternal-infant immune dyad in the context of maternal immunisation using the unbiased, systematic approach of systems biology proposed here. Our findings promise not only to unveil the mechanisms related to maternal immunisation but to identify pathways to target to improve the developmental trajectory and well-being of all children in general.

## Methods and analysis

### Study design

This is a prospective, observational cohort study.

### Study sites and sample size

There are four maternity services participating in this project- two private and two public. Together these services have over 25,000 births per year, of which half are primigravid women.

### Private health service partner involvement

In this project we partner with both public and private providers of antenatal care. In Australia almost one quarter of births occur in the private sector although this group is rarely included in research. It is essential to consider the private sector to maximise the opportunities for translation of key findings and to ensure broad representation of women so findings can be generalizable.

### Consumer and community involvement

Miracle Babies is Australia’s leading organisation supporting premature and sick newborns, their families and the hospitals that care for them. They are partnering on this project and will be providing input end-to-end for this study. This includes providing consumer representation on the project steering committee, design and review of the study protocol, review of the conduct and progress of the study, interpretation of the data and most importantly appropriate and sensitive dissemination of the findings.

### Inclusion criteria

A pregnant woman will be eligible for inclusion in the PREMITUR study if the following criteria are met

NulliparousAged 18 to ≤45 yearsGestation between 9 and 22 weeks at time of recruitmentWilling and able to comply with all study requirements including timing and/or nature of required assessments and follow up of mother and baby to six weeks post-partum

### Exclusion criteria

A pregnant woman will be ineligible for inclusion in the PREMITUR if the following criteria apply:

MultiparousMultiple pregnancyRisk factors for PTB e.g. previous cervical procedure such as cone biopsyUnable to provide consentConcomitant immunosuppressive medication likely to continue beyond first trimesterAny other significant acute or chronic medical condition that in the opinion of the investigator may interfere with the interpretation of study results or place the participant at increased risk if they participate in the study.Unwilling and unable to comply with all study requirements including timing and/or nature of required assessments and follow up of mother and baby to six weeks post-partum (e.g. planning to relocate during pregnancy)

### Recruitment and procedures

We aim to recruit 400 healthy nulliparous women over three years. We are restricting our recruitment to primigravid women.

Potential participants will be identified by one of two mechanisms. In the public system women will be identified from clinic lists as eligible by a research midwife who will alert the treating clinician. If deemed appropriate the treating clinician will introduce the study to the participant and seek their interest. If they are interested to receive further information then their details will be shared with the research midwife who will contact them, provide further information, answer questions and provide the participant information and consent form (PICF). Signed consent can be obtained either electronically or in paper form with a wet ink signature. A similar process is followed for women receiving private maternity care, although in this case identification of eligible women is via the private obstetrician (**Figure 1**).

**Figure 1 f1:**
[figure not shown]
Study Design (Created with BioRender.com).

Clinical data will be collected at baseline including established risk factors for PTB as well as past vaccination history. Pregnancy outcomes will be collected at birth. Venous blood (5mL) will be collected at each timepoint: 10-14 weeks, 20-22 weeks, 26-28 weeks, 34-36 weeks, and at birth (**Figure 2**).

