### Sample collection, processing, storage and data generation

Specifically, blood will be collected for transcriptomic (RNASeq) as well as epigenetic (methylation) analysis and plasma harvested for proteomics (via Somalogic Inc.) and metabolomics (via Metabolon Inc.). Cell composition of this blood sample will also be assessed by flow cytometric analysis capturing most innate and adaptive immune subsets, from neutrophils, dendritic cells (DCs) and their subsets, to NK cells, monocytes, as well as most T cell subsets and B cell subsets. The Paxgene tube will be used for transcriptomics. As little as 55 microlitres of blood is required for proteomics and metabolomics, so 5mL per timepoint is sufficient for the proposed testing. Given the longitudinal nature of our study set up, samples will be batch randomized to reduce artifact, as well as corrected using ComBat batch to normalise across multiple analytical runs. Following distributional normalisation, we will apply the full power of longitudinal samples from the same participants, i.e., features will be normalised as change over time within each woman, using the WithinVariation function implemented in the R *mixOmics* package. With this, absolute values will be represented as relative change over time - i.e. biological trajectories. We will analyse multiomic signatures across women to define the immune trajectory of pregnancy. We will then contrast omic signatures across clinical groups (healthy term vs. PTB).

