#### Analysis plan

##### Aim 1

We will compare the immune trajectory of all women with a preterm birth (estimated to be 8% of our total sample size) with a matched control group of women who deliver at term. We will not be performing multiomics on all participants recruited. To assess the immune trajectory in relation to pregnancy outcome longitudinally over time we will identify features both in the univariate and multivariate space. For univariate analysis, differentially expressed (DE) genes, proteins, or metabolites will be identified using DESeq2 v1.26. Correction for multiple comparisons will be done to control for false discoveries, filtering results based on a highly conservative p-value for significance (<0.001). Sparse Partial Least Squares - Discriminant Analysis (sPLS-DA) will be used to identify discriminatory features that co-vary with each other. Given the user-defined sparsity feature of sPLS-DA, and with the readout being classification accuracy, no p-value adjustment is necessary for this method. To assess the data in their biological context, i.e. integrated multi-omics, we will use two complementary integration strategies. *NetworkAnalyst* is based on known protein-protein interaction (PPI) networks and *DIABLO*, part of the *mixOmics* framework, a data-driven multi-omic integration approach. Given that *DIABLO* selects features that allow maximum class distinction (i.e. accurate classification of pregnancy outcome), this approach will also identify the earliest point during pregnancy that can accurately predict an adverse birth outcome. Finally, time course analyses that generate smoothing splines allow identification of groups of features that follow the same trajectory in a multivariate space. The *DynOmics* toolbox is an extension of the *mixOmics* toolbox used for multi-omic datasets built to identify these dynamic longitudinal changes in biological systems, while integrating multi-omic data.

##### Aim 2

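### Aim 1's within-woman normalisation over a schedule ending at birth can make gestational age look like a preterm-birth signature

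*Protocol article*

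**What the plan says.** The sampling schedule (Recruitment and procedures) has four windows fixed by gestation and a fifth fixed by an event: "Venous blood (5mL) will be collected at each timepoint: 10-14 weeks, 20-22 weeks, 26-28 weeks, 34-36 weeks, and at birth".

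Under Sample collection, processing, storage and data generation, the processing is also fixed: "features will be normalised as change over time within each woman, using the WithinVariation function". The group comparison follows: "We will then contrast omic signatures across clinical groups (healthy term vs. PTB".

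The Aim 1 analysis plan compares all PTB women "with a matched control group of women who deliver at term". The matching factors are not named. The methods listed are DESeq2, sPLS-DA, network and DIABLO integration, and smoothing-spline time courses whose time axis is not stated. For DIABLO the plan adds that "this approach will also identify the earliest point during pregnancy that can accurately predict an adverse birth outcome". The Rationale says of the underlying biology: "Pregnancy induces rapid changes in systemic maternal immunity".

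No stated step sets the birth sample apart from the other four.

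**The concern.** Outcome group fixes when the fifth sample is taken. Preterm women give it before term and controls give it at term, so gestational age at that sample does not overlap between the groups. Matching on women's characteristics cannot create overlap, and adjustment could only extrapolate. The 34-36 week sample exists only for women still pregnant, so births before 34 weeks drop out of it.

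The normalisation then spreads the problem. If each value is expressed relative to a woman's own average, that average is taken over an earlier or shorter series in PTB women. Visits that were aligned by gestation in the raw data become misaligned after centring.

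At stake is the Aim 1 conclusion: features that only track gestation could be reported as part of the trajectory leading to PTB. The search for the earliest predictive time point is exposed too, because a centred 10-14 week value contains information from samples taken later, including the one at birth.

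**Working it through.** **The plan's own figure.** 400 × 0.08 = 32 expected PTB cases, as stated. The claim of 80% power at 20 per group cannot be reproduced, because no effect size or SD is given.

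**Cases without a 34-36 week sample.** The share of the 32 delivering before 34 weeks is not given. At 10%, 20%, 30% and 40% (assumed), 3.2, 6.4, 9.6 and 12.8 women lack the sample, leaving 28.8, 25.6, 22.4 and 19.2.

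**Effect of centring.** I read the normalisation as subtracting each woman's own mean. Take a feature that rises linearly with gestation and illustrative sampling weeks.
- Term, birth at 39.5: (12 + 21 + 27 + 35 + 39.5)/5 = 26.9 weeks.
- PTB at 35.5: (12 + 21 + 27 + 35 + 35.5)/5 = 26.1. Every antenatal value shifts by 26.9 − 26.1 = 0.8 week of trend.
- PTB at 31, no 34-36 week sample: (12 + 21 + 27 + 31)/4 = 22.75. The shift is 4.15 weeks of trend.
- At birth, the raw gaps are −4.0 and −8.5 weeks. After centring they are −3.2 and −4.35, so centring reduces the gap there without removing it.

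**False positives with no PTB effect.** All inputs here are assumptions. Total SD is 1 and within-woman correlation 0.5. Antenatal samples fall uniformly within their windows, and term births uniformly over 37.5-41 weeks (mean 39.25). PTB births follow one of three mixes:
- 10% before 34 weeks (uniform 28.5-34, the rest 34.5-37): mean 0.1 × 31.25 + 0.9 × 35.75 = 35.3, gap 3.95 weeks;
- 30% before 34 weeks: mean 34.4, gap 4.85 weeks;
- uniform 30-37, so 4/7 = 57% before 34 weeks: mean 33.5, gap 5.75 weeks.

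For the uncentred birth sample, difference = drift × gap, and the rate at p<0.05 is about Φ(difference × √(n/2) − 1.96). At 0.1 SD/week:
- n = 20, gap 3.95: 0.395 × 3.162 − 1.96 = −0.71, about 24%;
- n = 32, gap 5.75: 0.575 × 4 − 1.96 = 0.34, about 63%.

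Simulated two-sample t-tests (6,000 studies per setting) agree, at 23% and 60%. The table gives the lowest and highest rate over the three mixes and n = 20 or 32 per group.

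| Drift, SD/week | Birth, uncentred, p<0.05 | Same, p<0.001 | Birth, centred, p<0.05 | 10-14 weeks, centred, p<0.05 | Same, p<0.001 |
|---|---|---|---|---|---|
| 0 | 5% | 0.1% | 4-5% | 5-6% | 0.0-0.2% |
| 0.05 | 9-21% | 0.5-1.5% | 9-15% | 6-15% | 0.2-0.6% |
| 0.1 | 23-60% | 1.5-13% | 22-43% | 11-42% | 0.4-5.5% |
| 0.2 | 66-99% | 15-82% | 63-94% | 28-91% | 2.5-46% |

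The uncentred 10-14 week sample stays at about 5% throughout. So does the 10-14 week sample when centring uses only the first three visits (4.6-5.7%). The unequal series therefore cause the spill-over.

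**Sensitivity to the SD unit.** If drift is stated per within-woman SD, with an equal between-woman SD (total √2 = 1.41), then 0.1 corresponds to 0.07 total SD per week. With 32 per group and 10-30% before 34 weeks, the uncentred birth sample then gives 21-27% at 0.1 and 59-73% at 0.2 (p<0.05).

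**The case against.** A reader might infer that the groups will be compared visit by visit, and that gestation will therefore be mistaken for a PTB signature. The article does not say that. The splines could run on actual gestational age, the matching factors are unnamed, and a condensed article may leave both to the full protocol or analysis plan. Their absence is not the point here.

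Three further objections have weight. The 10-14, 20-22 and 26-28 week windows sample both groups at like gestation, and prediction depends on antenatal samples. A t-test on one feature is only a stand-in for the listed methods. The drift rates and birth-week mixes are assumed, and the 57% mix is heavy on early PTB. The planned p<0.001 filter also lowers the rates considerably: at 0.1 SD/week the uncentred birth sample falls to 1.5-13%.

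What remains is what the article does state: the schedule, the within-woman normalisation and the term-versus-PTB contrast. A gestational time axis alone would not repair these. Centred PTB values would still sit 0.8 to 4.15 weeks of trend away from term values at the same gestation in the illustrations above. The strict threshold lowers how often the bias is declared but leaves the bias itself, which is declared more often as groups grow. If the normalisation were change from a first sample instead of from a woman's mean, this spill-over to earlier visits would not arise. The birth-sample confounding would.

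**Conclusion.** The concern holds as a built-in risk of bias, not as a certain error. Confounding of PTB with gestational age is unavoidable in an unadjusted contrast of the birth samples. At earlier visits it depends on centring, on how strongly a feature drifts with gestation, and on how many cases deliver early. A feature with no gestational drift is unaffected. The article describes the immune changes of pregnancy as rapid but gives no rate, so the tabulated rates show how sensitive the analysis could be and do not forecast this study's error rate. The documents do not support saying that all five visits are confounded in the raw data, or that the investigators have chosen a nominal-visit analysis.

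**What to change.** Amend the Aim 1 wording as follows.

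1. Take the birth sample out of the primary PTB-versus-term contrast and out of the within-woman normalisation. Report it descriptively, as confounded with gestation.
2. Normalise on antenatal visits available in both groups, or truncate each matched control's series at her case's delivery gestation before normalising.
3. Use actual gestational age at sampling as the time axis.
4. Limit the 34-36 week contrast to women still pregnant, and state that it covers late PTB only.

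Do not replace the birth contrast by setting a PTB birth sample against a control's antenatal sample. That exchanges a gestation difference for a delivered-versus-undelivered one, and the Introduction itself links preterm labour to inflammatory processes.

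The cost is that birth samples leave the primary Aim 1 contrast. The change is to analysis wording, and no new samples are needed.

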We will compare the immune trajectory of 20 unvaccinated women with 20 women who received either one of the two vaccines recommended in pregnancy, and 20 vaccinated with both vaccines. Recruitment started prior to the availability of COVID-19 vaccines but continued during the rollout of COVID-19 vaccines. Data on any vaccination during pregnancy is captured and will be taken into account in the analysis. Based on our previous work, we expect ~10 women in our cohort to choose to not be vaccinated at all, and approximately 50 women to be vaccinated with either influenza or pertussis alone. If we are unable to recruit 10 controls who have received no vaccination we intend to use women who are vaccinated late in pregnancy as a control over the time periods they remain “unvaccinated”. We will employ the same blood processing and data analysis pipeline summarised for Aim 1.

##### Aim 3

Samples will be obtained on day of life 1 and 6 weeks of life (day of recommended first follow up) via our highly standardised, non-invasive thus non-painful sampling procedure (Nasosorption), well-tolerated by newborn infants (and their parents) as described. We will process and analyse these 120 samples as described above contrasting the infants’ immune trajectory as a function of maternal immunisation status.

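### Within-woman normalisation does not exclude the birth draw, which is one time point regardless of labour; under subject-mean centring, outcome-time information enters the antenatal values used to find the earliest predictor

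*Protocol article*

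**What the plan says.** - Recruitment and procedures (text under Figure 1) sets the first two draws at 10-14 and 20-22 weeks and the other three at "26-28 weeks, 34-36 weeks, and at birth". The first four have gestational windows. The fifth is defined by the event alone.
- Sample collection, processing, storage and data generation states that "features will be normalised as change over time within each woman, using the WithinVariation function" from the mixOmics package, so that "absolute values will be represented as relative change over time - i.e. biological trajectories". No draw is left out of this step.
- Analysis plan, Aim 1 compares all preterm births "with a matched control group of women who deliver at term". The matching factors are not named, and preterm birth is not divided into spontaneous and provider-initiated. Of the DIABLO classifier it says that "this approach will also identify the earliest point during pregnancy that can accurately predict an adverse birth outcome".
- Analysis plan, Aim 2 compares groups of 20 by vaccination status and adds: "We will employ the same blood processing and data analysis pipeline summarised for Aim 1".
- The study is an observational cohort, so nothing in the design balances labour status between groups.

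**The concern.** Some women reach the birth draw in or after labour. Others are delivered without labour, for example by planned caesarean. If labour changes a blood feature, the birth draw mixes two states under one label.

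The normalisation can carry that mixture backwards. When a value is expressed as its distance from the woman's mean over all her draws, a change at birth alters the mean and hence every earlier value. An antenatal value built this way could not be computed at the antenatal visit, because it needs a sample taken at delivery. A classifier trained on such values cannot show that an outcome was predictable at 10-14 or 20-22 weeks, because part of what it reads comes from the delivery itself.

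At the birth draw, a group difference may reflect who laboured and not preterm birth or vaccination. If the groups have the same share of labouring women, there is no such bias, but the unmodelled mixture adds variance.

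**Working it through.** **The plan's own figures.** 400 x 0.08 = 32 expected preterm births, as stated. The plan gives 20 per group, 80% power and two-sided alpha 0.05, but no effect size. For a two-sample t-test these imply a difference of 0.909 SD.

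**Assumptions (not in the article).** The within-woman step is subtraction of the woman's mean over her draws. Labour shifts a feature by L = 1 to 2 within-woman SD, at the birth draw only. The share who laboured differs by 30 points: 80% v 50%, or 100% v 70% (every preterm woman laboured, 70% of term controls did).

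**Algebra.** Let a woman have T draws, with L added to the last. Her mean rises by L/T. Each antenatal value therefore moves by -L/T, and the birth value by L(1 - 1/T).
- T = 5: antenatal -0.20 L, birth +0.80 L.
- T = 4 (delivery before the 34-36 week draw): antenatal -0.25 L, birth +0.75 L.

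With shares p1 and p2 who laboured, the false antenatal gap between groups is -(L/T1)p1 + (L/T2)p2.
- 80% v 50%, five draws each: -0.20 x 0.30 x L = -0.06 SD (L = 1) to -0.12 SD (L = 2).
- 100% with four draws v 70% with five, L = 2: -0.50 + 0.28 = -0.22 SD.
- 80% in both groups, four v five draws: -0.05 x 0.80 x L = -0.04 to -0.08 SD. Unequal numbers of draws are enough to create a gap.

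**Simulation.** 20 per group, independent unit-variance draws, no true group difference, t-test at one visit, 40,000 runs. Ranges are for L = 1 to L = 2, after centring on all draws.

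| Shares who laboured | Draws | Antenatal p<0.05 | Birth p<0.05 |
|---|---|---|---|
| 70% v 70% | 5 v 5 | 5% | 5% |
| 80% v 50% | 5 v 5 | 5.6% to 7.1% | 12% to 25% |
| 100% v 70% | 5 v 5 | 5.6% to 6.8% | 12% to 29% |
| 80% v 80% | 4 v 5 | 5.4% to 5.8% | 5.2% to 5.7% |
| 80% v 50% | 4 v 5 | 6.1% to 10.5% | 10% to 20% |
| 100% v 70% | 4 v 5 | 6.8% to 12.1% | 10% to 20% |

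At the plan's univariate cut of p<0.001, with a 30-point gap and five draws in both groups, antenatal rejection is about 0.1% to 0.2%, and birth-draw rejection about 0.5% to 2.3%, against a nominal 0.1%.

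**Variance with equal shares.** If a share q did not labour in either group, the SD at the birth draw is sqrt(1 + L²q(1-q)). For L = 1, q = 0.3 it is sqrt(1.21) = 1.10. For L = 2, q = 0.5 it is sqrt(2) = 1.41. Power for 0.909 SD at 20 v 20 falls from 80% to 72% and 51%. This is for a single uncentred birth-visit comparison, not for the whole trajectory analysis.

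**After the change.** With centring on the antenatal draws only, the antenatal gap is 0.00 and rejection about 5% in every 30-point scenario above. The birth draw still rejects in about 12% to 30%, so it needs its own treatment.

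**The case against.** Five points can be made on the other side.

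1. *The formula is assumed.* The article names a function and speaks of relative change; it does not give the calculation. If values were taken relative to the first draw, antenatal values would not move at all. This stands as a condition on the antenatal part. The birth draw is affected either way.
2. *The antenatal effect is small.* This stands for the inputs used. Rates of 13% to 24% with five draws appear only with a 90% v 50% split and L of 3 to 5 SD. The shift is also common to all of a woman's antenatal draws, so differences between those draws are unchanged. It does not answer the structural point: an antenatal predictor should contain nothing from delivery, whatever the size.
3. *The article does not say that labour at term shifts blood features.* A reader might infer that it does. The Introduction reports that some studies link inflammatory processes to the early start of labour in preterm cases. That is inflammation before preterm labour, and it gives no L. This stands.
4. *Bias in the vaccine contrast is not shown.* A reader might infer that Aim 2 is confounded by labour. That needs labour share to differ by vaccine group, which the article neither shows nor rules out. This stands.
5. *The article is condensed.* Mode of birth may be recorded among the pregnancy outcomes, and the procedures figure is not available here. It cannot be said that labour status goes uncollected. But the time points, the normalisation and the earliest-point claim are all stated, and the problem comes from those choices together.

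**Conclusion.** The point holds in a limited form. As stated, the pipeline does not keep the birth draw out of the within-woman normalisation. If that step is subject-mean centring, each antenatal value carries -L/5 (or -L/4) of whatever happened at delivery. This undermines the earliest-predictor claim in Aim 1 in principle. Its effect on antenatal false positives is modest under the assumptions used: about 5.5% to 7%, and up to about 12% when preterm women have four draws and L = 2. At the birth draw, a 30-point gap in labour share gives about 12% to 30% false positives after centring with five draws in both groups. All these rates rest on assumed L and labour shares.

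The documents do not support the stronger readings that the vaccine contrast is biased, or that antenatal values are heavily contaminated. With equal labour shares and equal numbers of draws, labour adds variance and no bias.

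**What to change.** 1. Compute each woman's normalising mean from her antenatal draws only. For the prediction analysis, use only draws up to the time point being assessed. At the first draw a centred value is then zero by construction, so that time point has to be judged on unnormalised values.
2. Analyse the birth draw separately from the antenatal trajectory.
3. Code each birth draw as before labour, in labour or after delivery. Report the birth-visit contrasts in Aims 1 and 2 by that code, or adjusted for it, as a sensitivity analysis.
4. Do not make labour status a mandatory covariate or a matching rule. Under the study's own hypothesis it may lie downstream of vaccination, and it is part of the preterm birth outcome, so conditioning on it could remove the signal sought. With about 10 unvaccinated women expected, there is also little room to match.

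The cost is one data field, a little more analysis and a slightly noisier normalising mean (error variance 1/4 of a single draw's, against 1/5, for a woman with all draws). The change does not deal with features that trend over gestation when women have unequal numbers of antenatal draws; limiting the mean to draws up to the assessed time point helps there.
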